### Sample size

This study utilized a sample size calculation formula designed for comparing means between two independent groups. Our preliminary pilot-study data indicated a Simpson index of 0.8 in the OFS + AI group and 0.1 in the OFS + TAM group, with an effect size of *δ* = 0.7. Based on the literature-reported standard deviation of vaginal microbiota diversity (*σ* = 0.2), the effect size was calculated as d = δ/σ. The significance level was set at *α* = 0.05, with a statistical power of 1 - *β* = 0.8. The calculations suggested that 25 participants per group were necessary to detect a moderate effect size difference. Based on an annual cohort of 500 breast cancer patients, 20–30% (100–150 patients per year) are younger than 50 years. Over our planned 2-year recruitment period, we expect 200–300 eligible patients. Assuming a conservative recruitment rate of 40–50%, this allows us to successfully meet our target sample size of 110 participants (55 participants per group).

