### Cohort classification

This study employed an observational prospective cohort design with non-randomized grouping based on real-world clinical practice. Patients were categorized into two groups according to the endocrine therapy regimen prescribed by their treating clinicians, taking into account individual disease characteristics, age, prior treatment history, and personalized clinical needs. The prescription of OFS + AI versus OFS + TAM is determined by the treating oncologist in accordance NCCN (3) based on clinicopathological risk factors. In brief: (1) OFS + AI is preferred for patients at high risk of recurrenceor those with contraindications to tamoxifen; (2) OFS + TAM is considered for patients with intermediate risk or those who cannot tolerate AI; (3) Patient preference and comorbidities (e.g., baseline cardiovascular risk, endometrial abnormalities) are taken into account. Any patient using oral contraceptives or levonorgestrel-releasing IUDs is required to discontinue/remove them prior to enrollment, since hormone receptor-positive breast cancer is a contraindication for systemic or local hormonal contraceptives.

To assess and address potential confounding, comprehensive baseline data were collected, including demographic characteristics (age, BMI, educational level, marital status), clinicopathological features (tumor size, lymph node status, TNM stage, histological grade), immunohistochemical markers (ER, PR, HER2 expression status, Ki-67 index), treatment-related factors (surgical approach, chemotherapy history, radiotherapy history), and laboratory parameters (estrogen levels). Patients who received (neo) adjuvant chemotherapy are eligible for inclusion. By strictly enforcing the hormonal inclusion criteria (FSH < 40 IU/L and Estradiol >20 pg./mL), we ensure that even patients with prior chemotherapy exposure are in a biochemically confirmed premenopausal state at baseline. For these patients, baseline sampling and assessment are performed at least 4 weeks after the last chemotherapy dose and prior to the initiation of endocrinotherapy. Chemotherapy history (regimen, number of cycles, dates) is recorded as a potential confounder, and subgroup analyses stratified by chemotherapy exposure will be performed.

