A propensity score for receiving OFS + AI versus OFS + TAM will be estimated using a multivariable logistic regression model incorporating key baseline covariates, including age, BMI, tumor stage, prior chemotherapy exposure, and baseline ovarian function. Inverse Probability of Treatment Weighting (IPTW) will be used as the primary approach to balance baseline characteristics between the two groups. Stabilized weights will be calculated, which are truncated at the 1st and 99th percentiles to mitigate the influence of extreme weights. Standardized mean differences (SMD) will be assessed to confirm covariate balance, with an SMD < 0.1 considered acceptable.

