### Statistical analysis

This study utilized both the full analysis set (FAS) and the per-protocol set (PPS) for statistical evaluation. The FAS will include all enrolled participants who receive at least one dose of treatment and provide baseline data, analyzed according to their assigned group to minimize selection bias. The PPS will comprise participants who complete the study per protocol, excluding those with major violations such as non-adherence to treatment or loss to follow-up exceeding predefined thresholds. All tests will be two-sided, with a significance level of *α* = 0.05. Descriptive statistics will summarize continuous variables as mean ± standard deviation for normally distributed data or as median (interquartile range) for skewed distributions. Categorical variables will be presented as frequencies and percentages.

Given the observational nature of this cohort study, baseline imbalances between groups will be assessed using standardized mean differences. If substantial imbalances are detected (standardized mean difference >0.1 for key covariates), propensity score matching will be applied to create balanced subgroups for comparative analyses, with propensity scores estimated via logistic regression incorporating variables such as age, BMI, tumor stage, hormone receptor status, and chemotherapy history.

Between-group comparisons will use independent samples t-tests or Mann–Whitney U tests for continuous variables, depending on data distribution and variance homogeneity. Chi-square or Fisher’s exact tests will be applied for categorical variables.

For longitudinal analyses, we plan to use linear mixed-effects models (LMM) for continuous clinical outcomes (e.g., GSM symptom scores) and generalized linear mixed models (GLMM) for microbiome features (e.g., relative abundance of key taxa). Therapy group, time point, and their interaction will be included as fixed effects to evaluate whether temporal trajectories differ by treatment type. Repeated measures ANOVA (RM-ANOVA) will be retained only as a secondary sensitivity analysis for complete-case datasets. If the proportion of missing data for a given outcome exceeds 10%, multiple imputation by chained equations (MICE) will be performed under the missing-at-random (MAR) assumption, with 20 imputed datasets and pooled estimates using Rubin’s rules.

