Multivariable analyses will incorporate multiple linear regression and mixed-effects models, adjusting for confounders such as age, body mass index (BMI), tumor stage, hormone receptor status, and chemotherapy history. Stepwise regression will select variables to evaluate the independent effects of endocrine therapy regimens on vaginal microbiota changes. To address multiple comparisons across primary and secondary outcomes, Bonferroni correction will be applied where appropriate. Pre-specified subgroup analyses will be conducted, stratified by factors such as chemotherapy history and baseline estrogen levels, to explore heterogeneity of effects. Sensitivity analyses will verify result robustness, and subgroup findings will be interpreted cautiously as exploratory. All statistical analyses were executed using SPSS version 26.0 and R version 4.0 software.

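### Stepwise selection makes the adjustment set for the non-randomised regimen comparison data-driven, which can bias an unweighted estimate and makes its p-values and intervals too optimistic

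*Protocol article*

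**What the plan says.** All references are to the protocol article.

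- **Statistical analysis**, on the multivariable models: they will be fitted "adjusting for confounders such as age, body mass index (BMI), tumor stage, hormone receptor status, and chemotherapy history". The next sentence reads: "Stepwise regression will select variables to evaluate the independent effects of endocrine therapy regimens on vaginal microbiota changes". It gives no direction, no entry or removal criterion, and no covariates that are forced in.
- **Cohort classification**: the study has an "observational prospective cohort design with non-randomized grouping based on real-world clinical practice", and the treating oncologist chooses the regimen "based on clinicopathological risk factors". OFS + AI is preferred at high recurrence risk; OFS + TAM is considered at intermediate risk.
- **Cohort classification**, on confounding: "Inverse Probability of Treatment Weighting (IPTW) will be used as the primary approach to balance baseline characteristics between the two groups". The propensity model includes age, BMI, tumour stage, prior chemotherapy and baseline ovarian function. Weights are stabilised and truncated at the 1st and 99th percentiles.
- **Statistical analysis** adds propensity score matching if a standardised mean difference exceeds 0.1. It also specifies longitudinal mixed models with therapy group, time and their interaction as fixed effects.
- **Sample size**: "target sample size of 110 participants (55 participants per group").

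**The concern.** Two adjacent sentences define the adjustment differently. One names the confounders; the next lets the data remove any of them. Both cannot fix the adjustment set.

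Stepwise selection judges a covariate by how clearly it predicts the outcome in this sample. Confounding depends on two links, covariate to outcome and covariate to regimen. Regimen here follows recurrence risk, so tumour stage and chemotherapy history plausibly have a strong link to regimen. If their link to the microbiome is only moderate, they may fail the selection test in a sample of this size, and part of their effect then passes to the regimen coefficient. In addition, the standard error printed for the final model treats the selected set as if it had been chosen in advance, so intervals are too short and p-values too small.

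At stake is the comparison of OFS + AI with OFS + TAM on the primary outcome domain, which is a stated aim of the study.

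**Working it through.** The plan gives no figure on this point, so there is none to reproduce. The check asks what stepwise selection does at the planned size.

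**Inputs from the article.** n = 110, 55 per group (Sample size). "The significance level was set at" 0.05 (Sample size). "All tests will be two-sided" (Statistical analysis). Five named confounders.

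**Assumed inputs, not in the article.** Confounder strengths, their correlation, and the selection rule. The regimen term is forced in and its true effect is zero.

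**Step 1: why a real confounder fails the test.** For a standardised covariate and residual SD 1, the standard error of its coefficient is roughly 1/√110 = 0.095. The expected t-ratio is effect/0.095:

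- 0.12 SD: 0.12/0.095 = 1.26
- 0.21 SD: 0.21/0.095 = 2.21
- 0.30 SD: 0.30/0.095 = 3.16

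The two-sided 5% limit is about 1.98. Correlation with regimen and with other confounders lowers these ratios further.

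**Step 2: what dropping it does.** Omitting confounder k moves the regimen coefficient by β_k × δ_k, where β_k is its effect on outcome and δ_k its remaining mean difference between regimens. Its sign is the sign of the product.

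**Step 3: simulation A.** Two correlated confounders, log-odds 0.7 each on regimen; three null covariates; backward elimination at p < 0.05; unweighted; 2,000 datasets per row.

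| Confounder effect on outcome | At least one true confounder dropped | Type I error, stepwise | Type I error, all covariates kept |
|---|---|---|---|
| 0.12 SD | 98% | 10.7% | 4.6% |
| 0.21 SD | 85% | 9.4% | 5.6% |
| 0.30 SD | 51% | 8.1% | 5.4% |

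The Monte Carlo standard error at 5% is √(0.05 × 0.95/2000) = 0.5 percentage points.

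**Step 4: other rules and the planned weights, same set-up (correlation 0.3 assumed).**

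| Analysis | Bias (SD) | Type I error |
|---|---|---|
| Unweighted, backward p < 0.05 | 0.04 to 0.08 | 9-11% |
| Unweighted, backward p < 0.10 | not tabulated | 7.5-9.4% |
| Unweighted, AIC | not tabulated | 7.0-8.4% |
| Stabilised, truncated weights plus backward selection | at most 0.02 | 6-8% |
| The same weights without selection | not tabulated | 5-6% |

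**Step 5: simulation B, different assumptions.** Five independent confounders, each 0.10 to 0.30 SD on outcome and log-odds 0.3 to 0.5 on regimen; unweighted; backward (p > 0.10 out) and forward (p < 0.05 in).

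- True confounders dropped: 10% to 86%.
- Bias in the regimen effect: 0.015 to 0.167 SD with selection; -0.012 to 0.008 SD with the full model.
- Reported standard error relative to the actual spread: 4% to 18% too small. For example, 0.202 against 0.245 gives 1 - 0.202/0.245 = 18%.
- Type I error: 5.4% to 18.1% with selection; 3.5% to 6.1% with the full model.
- Least harm: all confounders at 0.30 SD with backward selection, type I error 5.4% to 7.8%.

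**Step 6: is selection needed to fit the model?** Intercept, regimen and five covariates make 7 coefficients; 110/7 = 15.7 women per coefficient. It is not.

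**The case against.** The strongest reply is that the stepwise model is not the only protection against confounding. IPTW is the stated primary approach to balance, with balance checks, and matching is a further provision. If the weights are carried into the stepwise model, confounding is largely removed before selection begins. This stands: bias falls to at most 0.02 SD, and the 8-11% in simulation A describes an analysis without weights. Two things survive. Type I error remains 6-8%, because selection still distorts the reported uncertainty. And the article does not say that the model meant to give the independent regimen effects is weighted.

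Second, the selection rule is not stated, so any figure for its harm is conditional. This stands too, which is why a range is given. The harm is small when every confounder is strong and the removal threshold is lenient.

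Third, a reader might infer that selection could remove the regimen term itself. The article does not support that: the sentence's purpose is to evaluate the regimen effect, and the longitudinal models keep therapy group as a fixed effect.

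Fourth, a reader might infer a bias in a known direction. The sign depends on how each confounder relates to the outcome, which is unknown, and several confounders may offset one another.

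**Conclusion.** The concern holds in a limited form. The article states affirmatively that the data will choose the variables for a non-randomised, indication-driven contrast, and this conflicts with its own list of confounders. At n = 110 this can drop true confounders, can bias the regimen estimate when the model is unweighted, and makes p-values and intervals too optimistic.

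With outcome effects of 0.12 to 0.30 SD, log-odds 0.7 on regimen and backward selection at p < 0.05 or p < 0.10, type I error is about 7-11% unweighted and 6-8% weighted, against about 5% with a fixed set. The alternative assumptions of simulation B widen the unweighted range to 5.4-18.1%. All of these rest on confounder strengths and selection rules that the article does not give.

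The documents do not support the stronger reading that the comparison will certainly be biased. They support the statement that the stepwise step adds avoidable risk and brings no needed gain in estimability.

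**What to change.** Delete the stepwise sentence. Specify one model containing regimen and a fixed covariate set, kept regardless of significance: the propensity variables in Cohort classification (age, BMI, tumour stage, prior chemotherapy, baseline ovarian function) plus the baseline value of the outcome. The last is an addition to the propensity list and should be stated as such.

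Treat hormone receptor status consistently. It appears in the matching and regression lists under Statistical analysis but not in the propensity model under Cohort classification. Overall positivity is constant by eligibility, but the criterion is ER and/or PR positive and the two are recorded separately, so the ER/PR pattern can vary. Either include it everywhere as that pattern or omit it everywhere.

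The cost is one sentence and a few degrees of freedom. With one term per covariate the model has 8 coefficients (intercept, regimen and six covariates): 110/8 = 13.8 women per coefficient, or 99/8 = 12.4 after the abstract's 10% attrition (110 × 0.9 = 99). A multi-level stage variable adds a few more terms. The change should be made before outcome data are examined.

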**Methods:**

This single-center prospective cohort at Women’s Hospital, Zhejiang University School of Medicine, will enroll 110 premenopausal women (18–45 years) with hormone receptor-positive breast cancer, allocated to OFS + AI or OFS + TAM based on clinical regimens. Vaginal swabs collected at baseline and 1, 3, 6, 12 months undergo 16S rRNA sequencing (V3-V4 region) with DADA2-based ASV analysis via QIIME 2 for species-level resolution. Assessments include Vaginal Health Index (VHI), GSM symptoms (VAS for dryness, dyspareunia, burning), s, and urinary symptoms (ICIQ-SF). Primary outcomes: microbiome diversity (Simpson index) and Lactobacillus abundance. Secondary: VHI, VAS, urinary scores. Analyses use repeated measures ANOVA and generalized estimating equations; sample size accounts for medium effect (*d* = 0.8) and 10% attrition. Ethically approved and registered in Chinese Clinical Trial Registry.

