### Primary outcome

This study identified vaginal microbial diversity and the relative abundance of Lactobacillus as the primary outcome measures. High-throughput sequencing of the 16S rRNA V3-V4 region was utilized, and bioinformatics analysis was conducted using the DADA2 pipeline via QIIME 2 to generate ASVs, enabling single-nucleotide resolution for quantitative assessment of alterations in vaginal microecological diversity. Species-level identification, particularly for Lactobacillus species, will be performed based on ASV taxonomic assignment. Simultaneously, the relative abundance of the Lactobacillus genus within the total bacterial community was analyzed to evaluate vaginal microecological homeostasis. Measurement time points were established at baseline, and at 1 month, 3 months, 6 months, and 12 months post-treatment, thereby creating a comprehensive longitudinal observation trajectory.

The collection of vaginal microbial samples followed a strictly standardized procedure: participants were instructed to abstain from sexual intercourse, vaginal medications, and douching for 48 h prior to sampling. Additionally, individuals who were menstruating were scheduled for sampling within a 3- to 7-day window following the cessation of menstruation to minimize interference from the menstrual cycle. During the sampling process, participants were positioned in the lithotomy position, and the cervix was fully exposed using a sterile vaginal speculum. A sterile cotton swab was rotated in the posterior vaginal fornix for a duration of 10 s, subsequently placed into a sterile tube containing DNA/RNA Shield preservative, temporarily stored at 4 °C, and then transferred to a – 80 °C ultra-low temperature freezer for long-term storage within 4 hours.

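### The Bonferroni rule pools primary with secondary outcomes and applies only where judged appropriate, so the level for a primary result is not fixed, and the sample size is set for one outcome at an undivided 0.05

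*Protocol article*

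**What the plan says.** The Primary outcome section of the protocol article has two outcomes: "This study identified vaginal microbial diversity and the relative abundance of Lactobacillus as the primary outcome measures". The Secondary outcomes section adds the Vaginal Health Index, VAS scores for dryness, dyspareunia and burning, and the ICIQ-SF. The abstract lists these as three measures; counted score by score they are five.

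The Statistical analysis section first sets a general level: "All tests will be two-sided, with a significance level of *α* = 0.05". Its last paragraph then says: "To address multiple comparisons across primary and secondary outcomes, Bonferroni correction will be applied where appropriate". No family, number of tests or adjusted level is given.

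The Sample size section rests on a single comparison: "This study utilized a sample size calculation formula designed for comparing means between two independent groups". The outcome is the Simpson index. "The significance level was set at *α* = 0.05", "with a statistical power of 1 - *β* = 0.8". The result is 25 per group, and the enrolment target is 110, or 55 per group. The abstract adds: "sample size accounts for medium effect (*d* = 0.8) and 10% attrition". No effect size is given for Lactobacillus abundance.

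**The concern.** A Bonferroni rule defines a significance level only once the family and the number of tests are known. Here neither is stated, and the qualifier leaves open whether the correction is used at all. Three readings fit the text: each primary at 0.05, each primary at 0.025, or each primary at 0.05 divided by the total of primary and secondary outcomes. A primary p-value between about 0.007 and 0.05 would count as positive or negative depending on a choice that can still be made once results are known.

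The literal reading has its own cost. If the secondary scores share the same alpha, adding a supportive score makes it harder to show an effect on a primary outcome. The Sample size section follows neither a pooled family nor the two primaries, because it uses one outcome and the whole 0.05.

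This matters because the Discussion intends the regimen comparison of Lactobacillus abundance and diversity to inform the choice of endocrine therapy. The error rule for those two outcomes should not be left open.

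**Working it through.** **Inputs.** Two-sided 0.05 and power 0.80 (Sample size, Statistical analysis); d = 0.8 and 10% attrition (abstract); 25 per group calculated and 55 per group planned (Sample size); two primary outcomes (Primary outcome). 55 × 0.9 = 49.5, so 49 evaluable per group.

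**Reproducing the plan's figure.** n per group = 2(z for 1 − α/2 + z for 0.80)² / d² = 2(1.960 + 0.842)² / 0.64 = 24.5, so 25 (26 by the t-test). The stated 25 therefore comes from the abstract's d = 0.8 with one test at 0.05. It does not come from the inputs in the Sample size section itself, where 0.7 / 0.2 = 3.5 would need only 2 per group (3 by the t-test). That mismatch is a separate matter. I use d = 0.8 because it is the effect that yields 25.

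**Candidate levels.**
- No correction: 0.05 for each primary.
- Two primaries: 0.05 / 2 = 0.025.
- Two primaries and three secondary measures, as the abstract counts them: 0.05 / 5 = 0.01.
- Two primaries and five secondary scores: 0.05 / 7 = 0.0071.

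**Error rate without correction.** For two primaries each at 0.05, the chance of at least one false positive is at most 0.05 + 0.05 = 10%. If they are independent it is 1 − 0.95² = 9.75%.

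**Power.** Two-sample t-test, d = 0.8, equal groups, 2n − 2 degrees of freedom, noncentrality d√(n/2). This is 0.8 × √12.5 = 2.83 at 25 per group, 0.8 × √24.5 = 3.96 at 49, and 0.8 × √27.5 = 4.20 at 55.

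| Tests | Level | n per group for 80% (normal / t) | t-based n with 10% attrition | Power at 25 | Power at 49 | Power at 55 |
|---|---|---|---|---|---|---|
| 1 | 0.05 | 25 / 26 | 29 | 79% | 97% | 99% |
| 2 | 0.025 | 30 / 31 | 35 | 70% | 95% | 97% |
| 5 | 0.01 | 37 / 39 | 44 | 56% | 91% | 94% |
| 7 | 0.0071 | 39 / 41 | 46 | 51% | 88% | 92% |

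Every required n in the table, with attrition added, is below the planned 55. By the same calculation 80% power holds for up to 20 Bonferroni tests at 49 per group and 43 at 55 per group.

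**Sensitivity to group sizes.** Regimens are prescribed, not assigned, so equal groups are a target and not a guarantee. Assuming 99 evaluable participants, a 33/66 split gives 93% power for two tests and 84% for seven; a 25/74 split gives 88% and 76%. These splits are assumptions. Weighting or matching would reduce the effective numbers further, by an amount the document does not allow one to calculate.

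**The case against.** Four points can be made for the plan.

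- **Power is not lost.** A reader might infer from the single-test calculation that the stated 80% is not delivered once Bonferroni applies. The documents do not support that. The falls to 70% and 51% belong to 25 per group, which is the calculated minimum and not the enrolment. At 49 or 55 evaluable per group with equal groups, power at d = 0.8 stays at 88% or more for all the named outcomes. Nor would it help to start from the smallest effect detectable with 49 per group at 0.05 (about d = 0.57). The plan does not state that effect, and any reduction in alpha then takes power below 80% by construction. This objection stands in full.
- **The statements are compatible.** A nominal 0.05 for all tests with a correction layered on it is common practice, and a sample size from one outcome with more than double the calculated number enrolled fits both. This stands: the sections do not strictly contradict each other. What is missing is the link between them.
- **Some control exists.** A reader might also conclude that the two primaries have no error control and run at up to 10%. That holds only if the Bonferroni sentence is not applied to them. The sentence names the primary outcomes, so the 10% is an upper bound under one permitted reading.
- **The family may be in a SAP.** Such detail often is, and the count of five or seven is mine. This stands in part. But the article does not defer the matter; it states a rule, and the rule both pools primaries with secondaries and makes its own use conditional. A SAP that followed it literally would inherit both problems.

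**Conclusion.** The point holds as a badly fixed multiplicity rule. On this document, the level at which a primary result counts as positive may be 0.05, 0.025 or about 0.007 to 0.01, and nothing stated prevents the choice from following the data. If the rule is applied as written, the primaries are tested at the pooled level. At 49 evaluable per group and d = 0.8 that means 88% power with seven outcomes, against at least 95% if alpha is kept to the two primaries.

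The sample-size statement is out of step with two primary outcomes: at 0.025 the minimum is about 31 per group rather than 25. The planned 55 covers this, so no loss of the stated power is claimed.

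These figures assume d = 0.8, roughly equal groups, 10% attrition and a plain two-sample comparison. They apply to a primary outcome with that effect. Power for Lactobacillus abundance cannot be checked, because no effect size is given for it. The matter should be corrected before analysis, but it does not call the size of the study into question.

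**What to change.** 1. Replace the Bonferroni sentence with a rule for the two primary outcomes only: Holm at an overall two-sided 0.05, or 0.025 each, on one stated contrast between regimens (for example, the difference at 12 months). Delete the conditional wording.
2. Test secondary outcomes only if both primaries succeed, with a correction such as Holm among themselves if confirmatory claims are wanted. Otherwise report them as supportive, with 95% confidence intervals.
3. Limit the general 0.05 statement in the Statistical analysis section so that it refers to this rule.
4. Restate the Sample size section at 0.025: d = 0.8 needs about 31 per group by the t-test, and 31 / 0.9 = 34.4, so 35 with 10% attrition. Say that 55 per group covers this.

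The cost is wording; no participants are added. The stated minimum becomes less favourable (31 instead of 25 per group), and no confirmatory claim on a secondary outcome is possible if a primary fails. Holm tests each primary at 0.025 or above, so power for each is at least 95% at 49 per group under the same assumptions.

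### Heterogeneity of the regimen effect is to be explored by stratified analyses, and no regimen-by-subgroup interaction is named to estimate it

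*Protocol article*

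**What the plan says.** The Statistical analysis section states both the purpose and the means: "Pre-specified subgroup analyses will be conducted, stratified by factors such as chemotherapy history and baseline estrogen levels, to explore heterogeneity of effects". The Cohort classification section repeats the means for one factor: "subgroup analyses stratified by chemotherapy exposure will be performed". The sentence after the first of these promises cautious, exploratory reading of subgroup findings.

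The same section sets the general testing rule: "All tests will be two-sided, with a significance level of *α* = 0.05". For the longitudinal analysis it plans mixed models with therapy group, time point and the product of the two as fixed effects. No term crossing regimen with chemotherapy history or baseline estrogen is named anywhere in the article.

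**The concern.** Whether the regimen effect differs between women with and without prior chemotherapy is a question about a difference of two differences. An analysis run separately in each stratum gives the two differences, but not the contrast between them or its uncertainty. The usual way to read such output, significant here and not there, mostly reflects the power of each stratum. It can suggest that an effect is confined to one subgroup when the effect is the same in both.

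Baseline estrogen raises a second, smaller issue. It is a continuous measurement and must be cut into classes before it can be stratified, which discards information that a continuous interaction would keep.

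At stake is the reading of the subgroup results. Chemotherapy-exposed women are eligible, chemotherapy history is recorded as a potential confounder, and regimen follows recurrence risk. The chemotherapy strata may therefore be unequal in size and in regimen mix, and unequal strata make discordant p-values more likely over most of the effect sizes considered here.

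**Working it through.** **Inputs from the article**
- Two-sided alpha of 0.05 (Statistical analysis).
- Power: "with a statistical power of 1 - *β* = 0.8" (Sample size).
- Standardised effect in the abstract: "sample size accounts for medium effect (*d* = 0.8) and 10% attrition".
- Raw effect and SD in the Sample size section: "with an effect size of *δ* = 0.7" and "standard deviation of vaginal microbiota diversity (*σ* = 0.2".
- Calculated size: "The calculations suggested that 25 participants per group were necessary to detect a moderate effect size difference". Target enrolment: 110, or 55 per group.

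**Assumptions (not in the article)**
- Two strata, split 50:50, 70:30 or 80:20, with the same split in both regimens.
- One outcome at one visit, compared by t-test within each stratum, unweighted.
- d = 0.5 as a smaller effect for comparison.

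**Step 1: the plan's own figure.** n per group = 2(1.960 + 0.842)² / d². With d = 0.8 this is 24.5, rounded up to 25, which reproduces the stated number. With 0.7/0.2 = 3.5 it is 1.3, rounded up to 2, which does not. So d = 0.8 is the effect size consistent with the stated 25, and it is the main case below.

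**Step 2: discordance under a common effect.** If p1 and p2 are the powers in the two strata, the chance that exactly one is significant is p1(1 − p2) + p2(1 − p1). Stratum powers come from the noncentral t distribution. Fractional stratum sizes are kept for the calculation.

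| d | Split | n per group in each stratum | p1 | p2 | Exactly one significant |
|---|---|---|---|---|---|
| 0.8 | 50:50 | 27.5 and 27.5 | 0.830 | 0.830 | 28% |
| 0.8 | 70:30 | 38.5 and 16.5 | 0.934 | 0.605 | 41% |
| 0.8 | 80:20 | 44 and 11 | 0.960 | 0.431 | 56% |
| 0.5 | 50:50 | 27.5 and 27.5 | 0.445 | 0.445 | 49% |
| 0.5 | 70:30 | 38.5 and 16.5 | 0.582 | 0.285 | 54% |
| 0.5 | 80:20 | 44 and 11 | 0.640 | 0.201 | 58% |

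Worked line (d = 0.8, 80:20): 0.960 × 0.569 + 0.431 × 0.040 = 0.546 + 0.017 = 0.563.

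**Step 3: sensitivity.**
- With 50 per group after roughly 10% attrition, d = 0.8 and an even split, the figure is 33%.
- At 55 per group with an even split it is 31% for d = 0.3 and 9% for d = 1.0.
- At d = 3.5 both strata have power of essentially 1, so the figure is near zero.

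**Step 4: the alternative.** A simulated regimen-by-stratum interaction test (40,000 runs per setting, equal strata, common effect) was significant in 4.9% to 5.1% of runs, whatever the size of the common effect.

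**Step 5: precision of the interaction.** On the standardised scale at one visit, SE = √(2/n1 + 2/n2), where n1 and n2 are the per-group sizes in the two strata.
- Even split: √(2/27.5 + 2/27.5) = 0.38, a 95% half-width of about 0.75.
- 80:20 split: √(2/44 + 2/11) = 0.48, a half-width of about 0.93.

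**The case against.** The strongest reply is that the article does not describe the faulty practice. It says that analyses will be stratified. It does not say that within-stratum p-values will be compared, and it does not rule out an interaction test. Stratum estimates shown beside an interaction test would fit the wording, and a condensed article may leave the test and any estrogen cut-points to a fuller plan. This stands. A reader might infer that the authors have chosen strata in place of an interaction, but the text does not support that. What remains is that stratification is named twice as the means and that no interaction is named for this purpose, although one is named for trajectories over time.

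A reader might also infer that a false single-subgroup finding would occur about half the time at this sample size. That holds for an even split only near d = 0.54, the effect for which 55 per group has 80% power, and the article gives no such effect. At its own d = 0.8 and an even split the figure is 28%. At the Sample size section's ratio of 3.5 it vanishes, although that ratio conflicts with the same section's description of a moderate effect and with its 25 per group.

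The exploratory label also counts. It limits how firmly a subgroup result may be claimed and keeps this point minor. It does not turn two stratum results into an estimate of their difference.

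Finally, a reader might link spurious subgroup effects to the Discussion's hopes for personalised choice of therapy. Those statements rest on the overall regimen comparison and a prediction model. They cite no subgroup result, so that link is not supported.

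**Conclusion.** The point holds as a minor one. The named method, stratified analysis, does not by itself estimate heterogeneity, and a better method fits the mixed model already planned. If strata were judged by their own p-values, a common effect would look confined to one stratum in about 28% to 56% of studies at d = 0.8 and in about 49% to 58% at d = 0.5, against about 5% for an interaction test. These figures assume 55 per group, splits from 50:50 to 80:20, and a single-visit t-test in each stratum. They would change under a weighted repeated-measures model and fall to near zero at a ratio of 3.5. They show the hazard of one way of reading the output, and the article does not say that it will be read that way.

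**What to change.** State that heterogeneity will be judged by a regimen-by-subgroup term in the planned mixed model, with the same confounder adjustment as the main comparison. Keep baseline estradiol continuous in that term. Report the interaction estimate with its 95% CI for each factor. Show stratum estimates with intervals descriptively, without within-stratum significance tests, and keep the exploratory label.

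No new data are needed. The cost in parameters is small if the interaction concerns a single regimen contrast. It grows if crossed with time: with five visits as categories, a binary factor adds 1 (regimen), 4 (time) and 4 (three-way) parameters, nine beyond its main effect. The interval will be wide with 110 women, as step 5 shows, so a non-significant interaction must not be read as evidence that the effect is the same in all women.
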